## Abstract

**Background:**

Radiation therapy is the method of choice for subjects with inoperable salivary gland malignancies. I-125 brachytherapy, delivering a high radiation dose to a tumor but sparing surrounding normal tissues, is supposed to be ideal modality for the treatment of salivary gland malignancies. We designed a randomised controlled clinical trial to compare the efficacy of I-125 permanent brachytherapy (PBT) versus intensity-modulated radiation therapy (IMRT) for inoperable salivary gland malignancies.

**Methods/Design:**

In this study, inclusion criteria are subjects with inoperable salivary gland malignancies, aged 18–80 years, have provided informed consent, with at least one measurable tumor focus, be able to survive ≥3 months, Karnofsky performance status ≥60, have adequate hematopoietic function of bone marrow, have normal liver and kidney function, and are willing to prevent pregnancy.

Exclusion criteria include a history of radiation or chemotherapy, a history of other malignant tumors in the past 5 years, receiving other effective treatments, participating in other clinical trials, with circulatory metastasis, cognitive impairment, severe cardiovascular and cerebrovascular diseases, acute infection, uncontrolled systemic disease, history of interstitial lungdisease, and being pregnant or breast feeding.

The study will be conducted as a clinical, prospective, randomised controlled trial with balanced randomisation (1:1). The planned sample size is 90 subjects. Subjects with inoperable salivary gland malignancies are randomised to receive either I-125 PBT or IMRT, with stratification by tumor size and neck lymph node metastasis. Participants in both groups will be followed up at 2, 4, 6, 9, 12, 15, 18, 21 and 24 months after randomization. The primary outcome is local control rate of the primary site (based on imaging findings and clinical examination, RECIST criteria) in 1 year. Secondary outcomes are progression-free survival, overall survival, quality of life (QOL) measured with the European Organization for Research and Treatment of Cancer QOL Questionnaire (EORTC QLQ-C30 and QLQ-H&N35) of Chinese version, and safety of treatment. Chi-squared test is used to compare the local control rates in both groups. The survival curves are estimated by the Kaplan-Meier method, and log-rank test is used to test the significant difference.

**Discussion:**

Only few observational studies have investigated the effect of I-125 PBT on inoperable salivary gland malignancies. To our knowledge, this is the first randomised controlled trial to investigate the efficacy of I-125 PBT for subjects with inoperable salivary gland malignancies, and will add to the knowledge base for the treatment of these subjects.

**Trial registration:**

The study is registered to Clinical Trials.gov (NCT02048254) on Jan 29, 2014.

## Background

Primary malignant tumors of the major and minor salivary glands are relatively rare entities, accounting for only about 3–5 % of all head and neck malignancies. They also contain a diverse group of histologies, with disparate characteristics in terms of aggressiveness and patterns of spread [1]. Surgery has historically been the mainstay of treatment for salivary gland malignancies. Subjects with low-grade tumors are usually treated with surgery alone if complete excision can be achieved. Radiotherapy, as a postoperative adjunct to surgery, has traditionally been reserved for subjects with microscopically high-grade tumors, positive margins or nerve invasion. Although carcinomas originating from the salivary glands were previously thought to be radioresistant, the role of adjunct radiotherapy in therapy has become well recognized [2, 3]. However, the therapy for inoperable malignant salivary has been extremely challenging in clinical practice: some subjects are either not candidates for definitive resection or undergo limited procedures leaving behind gross residual disease. Typically, these subjects are deemed inoperable because of technical issues related to the extensiveness or location of the primary tumor. Another subset of inoperable subjects present with medical comorbidities that places them at unacceptably high risk for perioperative complications. Lastly, some subjects refuse surgical therapy out of personal preference. For whatever reason, these inoperable subjects have all traditionally been offered definitive radiation therapy as an alternative to surgery. Unfortunately, the reported results following low linear energy transfer (LET) irradiation are poor, with overall local control rates average below 30 % [4–10]. In a multicenter randomised controlled study conducted by the American Radiation Therapy Oncology (RTOG) and the UK Medical Research Council (MRC), the 2-year local control rate (LCR) of unresectable salivary gland cancers with conventional external radiotherapy was only 17 % [10].

The dose response of biological systems is influenced by the LET of ionizing radiation. In general, relative radiobiological effectiveness (RBE) increases with LET. A number of studies have been carried out to investigate the effectiveness of high-LET RT such as fast neutron RT. Batterman et al. described an elevated RBE for fast neutrons in the treatment of lung metastases of malignant salivary gland tumors. In this study, the highest RBE values up to 8 were found for ACC [11]. The randomised controlled study conducted by RTOG and MRC showed that the 2-year local control rate was 67 % for fast neutron radiotherapy compared with 17 % for conventional photon radiation [10]. However, the indication of fast neutron radiotherapy has been strictly limited because of its unacceptable damage to the surrounding normal tissues [12, 13]. In heavy particles radiotherapy, carbon ions have similar radiobiologic properties as neutrons, and higher RBE values can be expected for salivary gland tumors. Compared with neutron RT, carbon ions additionally provide physical selectivity due to an inverse dose profile. Thus, carbon ions was considered to have potentially greater clinical value [14]. In Germany, intensity-modulated radiation therapy (IMRT) combined with carbon ions radiotherapy was recommended as the standard treatment for inoperable salivary gland malignancies [15]. But carbon ions radiotherapy was expensive and unavailable, which obviously limits its application.

Brachytherapy is an important modality in the treatment of human malignancy with ionizing radiation. Where applicable, it may be the method of choice for the following reasons [16, 17]. First, the localized dose distribution enhances the ratio of tumor dose to surrounding normal tissue dose. Second, the reduction of oxygen enhancement ratio and dose rate may partially circumvent the radioresistance of hypoxic tumor cells. Permanent implants of I-125 sources in focus sites have been widely used, especially for prostatic cancer [18]. Because LET increases with decreasing photon energy, I-125 source with low energy photons(average 28 keV) has higher RBE values (approximately 1.4) [19]. In addition, the low photon energy also provides more sparing for adjacent normal tissue and easy resolution of the problem of protecting medical staff from radiation exposure. Some studies have shown that I-125 permanent brachytherapy (PBT) may have potential advantages in local control of salivary gland malignancies and in minimizing radiobiological damage to normal adjacent tissues [20–24]. I-125 has a long half-life of 60 days and may be ineffective in eradicating tumors with fast growth kinetics [25–27]. The clinical efficacy of I-125 in prostatic cancer may be due to the relative slow proliferative rate of this disease [25–27]. Like prostatic cancer, many of salivary gland malignancies are characteristically slowly proliferating tumours with long natural histories. Therefore, I-125 is supposed to be ideal modality for the treatment of salivary gland malignancies, as suggested by other nonrandomised clinical trials. In order to obtain more credible evidence, we launch a Phase III, randomised controlled trial to compare the efficacy of I-125 PBT versus IMRT for inoperable salivary gland malignancies.

## Methods and design

### Trial design and setting

The study is conducted as a single center, prospective, randomised controlled trial with balanced randomisation (1:1) for subjects who have inoperable malignant salivary gland tumors are randomised to receive either I-125 PBT or IMRT. Subjects are stratified by tumor size (≤4 cm vs. >4 cm) and neck lymph node metastasis (yes vs. no). Subjects are recruited continuously by oncologists at Department of Oral and Maxillofacial Surgery, Peking University School and Hospital of Stomatology which is the only department to treating salivary gland malignancies by I-125 PBT in China.

### Ethical approval

The protocol and informed consent form have been reviewed and approved by the Institutional Review Boards of the Peking University Health Science Center in Beijing, China, and registered at www.clinicaltrials.gov (NCT02048254). Figure 1 illustrates the flow diagram of the study for both the intervention and control groups.

**Fig. 1 Fig1:**
[figure not shown]
Study flow chart

### Participants

Ninety subjects will be recruited for the study and divided into an intervention group (I-125 PBT) and a control group (IMRT).

### Inclusion criteria

In the study, inclusion criteria are as follows: (1) willing to participate and sign informed consent; (2) aged 18–80 years; (3) malignancies originating from major or minor salivary glands based on pathological and/or cytological diagnosis, including primary or recurrent tumors; (4) with inoperable tumors, including unresectable primary locally advanced tumors; unresectable recurrent tumors; and unable to undergo surgery due to other medical comorbidities or refusal of surgery out of personal preference, and being T3/T4 T-stage; (5) with at least one measurable tumor focus based on RECIST criteria and imaging diagnosis completed in 30 days before enrollment; (6) expected survival time ≥3 months; (7) Karnofsky performance status ≥60; (8) adequate hematopoietic function of bone marrow in previous 7 days: hemoglobin ≥9 g/dL, white blood cell count ≥3.0 × 10^9^/L, neutrophils count ≥1.5 × 10^9^/L, platelet count ≥100 × 10^9^/L; (9) normal liver and kidney function in previous 14 days: total bilirubin in serum ≤1.5 times the upper limit of normal (ULN), alanine transaminase and aspartate transaminase ≤3 times ULN, creatinine ≤1.5 times ULN; (10) willing to take measures to prevent pregnancy.

### Exclusion criteria

Exclusion criteria include: (1) with a history of radiation treatment on head and neck; (2) with a history of other malignant tumors in past 5 years, except for healed skin basal cell carcinoma and cervical carcinoma in situ; (3) with a history of tumor chemotherapy; (4) receiving other effective treatments; (5) having participated in other clinical trials in 4 weeks before enrollment; (6) with circulatory metastasis; (7) with the histology subtype of squamous cell carcinoma; (8) without measurable tumor focus, such as diffuse infiltrative carcinoma; (9) cognitive impairment due to neursis or psychosis; (10) cardiovascular and cerebrovascular diseases with clinical significance, such as heart failure in NYHA III/IV, uncontrolled coronary heart disease, myocardiopathy, uncontrolled arrhythmia, uncontrolled hypertension, history of myocardial infarction or cerebral infarction in the past half year; (11) severe clinical infection in 14 days before randomization including active pulmonary tuberculosis; (12) human immunodeficiency virus infection, active hepatitis B or hepatitis C; (13) uncontrolled systemic disease, such as diabetes mellitus; (14) with the history of interstitial lung disease, such as interstitial pneumonia, pulmonary fibrosis, or diagnosed as interstitial lung disease by chest X-ray/CT image; (15) being pregnant or breast feeding.

### Withdrawal of individual subjects

Subjects can withdraw from the study at any time for any reason without any consequences. The investigator can decide to let a subject out from the study for particular medical reasons, for example, serious adverse events. For every subject who decides to withdraw from the study, the reasons for withdrawal should be recorded.

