### Blinding

Allocation status cannot be blinded for the participants and investigators due to different treatment methods and the visibility of implanted I-125 seed in CT image. However, the primary outcome (response to treatment) will be evaluated by an independent assessment board. Further, all statistical analysis will be done by a statistician in Peking University Clinical Research Institute who is not affiliated with the trial.

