**Fig. 2 Fig2:**
[figure not shown]
Observation, assessment, and follow-up schedule

After randomization, eligible participants will receive their treatment planning investigations and are followed-up following the same schedule for both intervention group and control group (Fig. 2) until recurrence, other malignancy or death is confirmed. Treatment duration is approximately 6–7 weeks for IMRT group. All the participants in both groups will be followed up at 2, 4, 6, 9, 12, 15, 18, 21 and 24 months after randomization, with specialized examination, imaging examination, blood routine examination and biochemistry, Karnofsky performance scale, recording of treatment and adverse events assessment done each time. Quality of life (QOL) scale will be assessed at 2, 6, 12, and 24 months. Forward radiation adverse reactions will be evaluated at each follow-up appointment except at 2 months after randomization. In addition, pathological diagnosis and PET/CT examination will be considered by the investigator if imaging examinations are inadequate to assess the primary outcome. Radioactive adverse events were classified by The National Cancer Institute-Common Terminology Criteria for Adverse Events (NCI-CTCAE) 4.0 standard. Chronic radioactive damages were classified by the criteria of Radiation Therapy Oncology Group/European Organization for Research and Treatment of Cancer (RTOG/EORTC), with common signs and severity recorded.

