### Outcomes

Assessment of efficacy will be carried out by evaluation of imaging examination at each follow-up. If applicable, response to treatment will be evaluated according to the RECIST criteria (version 1.1) and classified as complete response (CR), partial response (PR), stable disease (SD) and progressive disease (PD). 

The primary outcome is estimated as the difference between the intervention and the control group in local control rate in 1 year. Local control rate is judged to have been attained if there is no evidence of PD at the primary site based on imaging findings and clinical examination at follow-up. However, distant metastasis and second primary cancer are not belonged to PD at the primary site in accordance with RECIST criteria (version 1.1) [28].

Secondary outcomes are a) progression-free survival (PFS), defined as the time from randomization to the earliest occurrence of PD in whole body or death due to any cause; PD in whole body includes PD at the primary site, distant metastasis and second primary cancer; b) overall survival (OS), from the date of randomization to the date of death from any cause or last date when the participant is alive; c) QOL evaluated using the European Organization for Research and Treatment of Cancer QOL Questionnaire (EORTC QLQ-C30 and QLQ-H&N35) of Chinese version; and d) safety of treatment.

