### Statistical analysis

Analyses will be made using SAS statistical software (version 9.3, SAS Institute, Cary, NC, USA) by researchers at the Peking University Clinical Research Institute. The primary analyses will be done on an intent-to-treat basis and the last observation carry forward (LOCF) is used for missing values. Descriptive statistics will be used to summarize demographic and clinical characteristics of subjects randomised to the intervention and control group. The difference between two groups on demographic and clinical characteristics, response rate and drop-out rate will be compared using t-tests (or Wilcoxon rank sum test) and chi-square test/Fisher’s exact test as appropriate.

Primary outcome (local control rate in 1 year) analyses will be carried out using chi-squared tests. The survival curves (PFS and OS) are estimated by the Kaplan-Meier method, and log-rank test is used to test the null hypothesis that the respective curves are equal between the two groups. A two-sided significance level of 5 % is used. A covariance model will be used to compare the QOL between two groups by adjusting the difference of baseline. The incidence of adverse events between two groups is compared with the chi-square test/Fisher’s exact test.

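### Investigators who know the arm may end a patient's study participation for medical reasons, and LOCF then scores anyone removed before local progression as locally controlled at 1 year

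*Protocol article*

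**What the plan says.** Five statements in the protocol article bear on this point.

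- **Withdrawal of individual subjects:** "The investigator can decide to let a subject out from the study for particular medical reasons, for example, serious adverse events". The section does not distinguish stopping treatment from stopping follow-up. It adds: "For every subject who decides to withdraw from the study, the reasons for withdrawal should be recorded". As worded, that covers patients who choose to leave and not clearly those whom the investigator takes out.
- **Blinding:** "Allocation status cannot be blinded for the participants and investigators". The same section says that "the primary outcome (response to treatment) will be evaluated by an independent assessment board".
- **Initial screening, assessment and follow-up:** both arms follow one visit schedule (2, 4, 6, 9 and 12 months within the first year) "until recurrence, other malignancy or death is confirmed". Adverse events are not listed as a reason to end follow-up.
- **Outcomes:** "Local control rate is judged to have been attained if there is no evidence of PD at the primary site". Complete response, partial response and stable disease therefore all count as control.
- **Statistical analysis:** "The primary analyses will be done on an intent-to-treat basis and the last observation carry forward (LOCF) is used for missing values".

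**The concern.** An intention-to-treat comparison at 1 year needs the 12-month primary-site status of everyone randomised, including patients with serious toxicity. The withdrawal rule allows those patients to leave the study by decision of someone who knows their arm. Two other stated rules then settle their result: LOCF carries the last response forward, and absence of progression counts as success. A patient removed after a visit showing response or stable disease, and before month 12, becomes a 1-year local control whatever happens to the tumour later. A patient removed after local progression stays a failure, so the conversion works in one direction only.

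If removals differ between arms, the primary difference is biased towards the arm with more of them. If they are equal, a true difference is diluted. PFS, OS and safety are affected by a different route: these patients' follow-up stops, and the censoring may be informative.

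**Working it through.** **Inputs.** From *Sample size estimation*: 1-year control of 81% (PBT) and 45% (IMRT), 90% power, two-sided 5%, 72 evaluable, 20% drop-out, 90 enrolled (45 per arm). From *Statistical analysis*: chi-squared test and LOCF. Assumed, because the article gives no figures: the share *w* of an arm removed before local progression (5, 10, 15%), removed patients having the same true control rate as the rest of their arm, and a common true rate of 60% for the no-difference case.

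**Step 1: the plan's own figure.** The usual two-proportion formula (pooled variance under the null, no continuity correction) gives 36 per arm, 72 in total; 72/0.8 = 90. The stated sample size reproduces.

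**Step 2: the rate after LOCF.** If a share *w* is removed before local progression and scored as controlled, the analysed rate is p(1 − w) + w. For IMRT with w = 0.10: 0.45 × 0.90 + 0.10 = 0.505. One such patient supplies 1/45 = 2.2 points of the arm's controlled share. On the plan's own rates, 55% of IMRT patients and 19% of PBT patients would in truth have failed by 1 year.

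**Step 3: difference and power.** Exact binomial power of the Pearson chi-squared test, 45 per arm. With no removals the difference is 36 points and power is 95.7%.

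| Removed | IMRT only: rates | Difference | Power | PBT only: rates | Difference | Both arms: difference | Power |
|---|---|---|---|---|---|---|---|
| 5% | 81% vs 47.8% | 33.3 | 92.7% | 82.0% vs 45% | 37.0 | 34.2 | 94.2% |
| 10% | 81% vs 50.5% | 30.5 | 88.4% | 82.9% vs 45% | 37.9 | 32.4 | 92.4% |
| 15% | 81% vs 53.3% | 27.8 | 82.4% | 83.9% vs 45% | 38.9 | 30.6 | 90.2% |

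**Step 4: no true difference.** With 60% true control in both arms and removal in one arm only, the analysed rates are 60% against 62, 64 or 66%. Type I error rises from 4.9% to 5.4, 6.8 or 9.2%. With equal removal the two expected rates remain equal, so no false difference arises; the exact size is 5.0, 5.2 or 5.3%, which only reflects the discreteness of the test as the common rate moves.

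**Step 5: can another rule rescue this?** The independent board limits biased reading of images, but it cannot assess an image that does not exist. The follow-up section could be read as keeping these patients under observation, but the withdrawal section says they leave the study. The two statements do not fit together as written.

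**The case against.** **The article is condensed.** Follow-up after withdrawal is often left to the full protocol, and the follow-up section can be read as continuing visits. That would answer a complaint about missing detail. Here, however, study exit and LOCF are both stated outright, and no later analysis document can recover scans that were not taken. What stands is that the passages may need only reconciling, not redesign.

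**The size is assumed.** The article gives no serious adverse event or removal rate by arm, so neither the amount nor the direction of bias is known. With equal removal up to 15%, power stays at or above the planned 90% and there is no type I inflation. This stands, and it limits the weight of the point.

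**Stronger readings that the text does not support.**

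- A reader might infer that a patient removed during the 6–7 weeks of IMRT has a baseline status carried forward as success, so that the rule specifically flatters IMRT. The article does not say what is carried forward before the 2-month visit, and local control is judged at follow-up. Nor is PBT free of later exposure to the rule: its dose accumulates over 6 months and re-implantation is possible.
- A reader might infer that LOCF also distorts PFS and OS. Those use Kaplan-Meier and log-rank methods, so the issue there is possibly informative censoring.
- A reader might infer that intention to treat is abandoned. Removed patients stay in their randomised arm; what is lost is their observed outcome.

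**Conclusion.** The point holds in a limited form. The withdrawal rule and the follow-up rule conflict. Combined with LOCF and a success definition based on absence of progression, the withdrawal rule scores patients removed before local progression as 1-year controls, on the decision of someone who knows the arm.

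Under assumed removal of 5 to 15% in one arm only, the 36-point difference moves to between 27.8 points (IMRT only, 15%) and 38.9 points (PBT only, 15%). Power in the IMRT-only case falls to 82.4% at the worst, and type I error at a common 60% reaches 9.2%. Equal removal dilutes the difference but gives no false positives. These figures rest on the removal shares, on removed patients resembling the rest of their arm, and on all of them leaving before any local progression is seen. The direction cannot be predicted from the document. The change should be made because it is cheap and protects the primary endpoint, not because a particular bias has been shown.

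**What to change.** In *Withdrawal of individual subjects*, state that an investigator's decision for a medical reason does not end study follow-up. Unless the patient withdraws consent, the patient stays on the schedule in *Initial screening, assessment and follow-up* for primary-site imaging, survival and toxicity. Extend the recording of reasons to investigator-led decisions. Decisions about treatment itself stay with the existing clinical text; nothing is proposed on them here.

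The cost is a short wording change and some extra effort to keep these patients attending visits that are already scheduled. The sample size does not change. The change does not cure LOCF for patients who withdraw on their own initiative, which is a separate issue.
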